##### Outcomes and measures

2.3.4.2

In module 3, primary and secondary outcomes will be collected, see Table 2.

**Table 2 T2:** Overview of outcomes of module 3 of the NODE study.

Outcome	Concept	Instrument/parameter	Time point of measuring & sample size
Primary outcome			
	Effectiveness of the care model	Proportion of patients that are actually treated (study arm 1 and 2)—or could have been treated (study arm 3) in an alternative outpatient emergency care model instead of in the ED	t0 (*n* = 1,031)
Secondary outcomes			
	Efficiency of care model	Proportion of cases who are actually treated in the alternative care structure without being referred back to the ED.	t0 (*n* = 1,031)
	Process quality	Process times (e.g., duration of treatment, time until diagnostic measures are available/discharge), frequency of diagnostic procedures	t0 (*n* = 1,031) & t1 (*n* = 344)
	Patient safety	Adverse events: Mortality, unplanned (re-)admission to the ICU, unplanned inpatient admission, unplanned re-attendance at the ED within 30 days	t0 (*n* = 1,031) & t1 (*n* = 344)
	Patient satisfaction	ZUF-8 (29)	t1 (*n* = 344)
	Health-related quality of life	EQ-5D-5l (34)	t1 (*n* = 344)
	Costs and Cost-effectiveness	Costs calculated based on utilization of: hospital stays, outpatient visits, inpatient stays, medication/pharmaceuticals, adjuvants and devices, diagnostic and therapeutic measures, total costs in relation to primary outcomes	t1 (*n* = 344)
	Further clinical outcomes (analysis depending on the sufficient number of cases)	Length of inpatient stay, frequency of ICU stay, length of ICU stay at t0 and t1, if applicable.	t0 (*n* = 1,031) & t1 (*n* = 344)

ED, emergency department; EQ-5D-5l, 5-level EQ-5D version of the EuroQoL group questionnaire; ICU, intensive care unit; ZUF-8, “Fragebogen zur Messung der Patientenzufriedenheit” = Zurich patient satisfaction questionnaire. T0 = baseline, t1 = follow up. Study arm 1 = hospital-owned separate outpatient care model within the ED premises or on the hospital grounds; study arm 2 = urgent care practice of the Regional Association of SHI Physicians at the ED location; study arm 3 = ED with standard care model and prospective assessment of patient-care and urgency levels by ED doctors.

##### Power calculation in module 3

2.3.4.3

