Study arm 1: Assumed frequency of the primary endpoint 30%—*n* = 323Study arm 2: Assumed frequency of the primary endpoint 50%—*n* = 385Study arm 3: Expected incidence of primary endpoint 70%—*n* = 323This gives a final sample size of *n* = 1,031. The aim is that approximately one third of the recruited patients (*n* = 344) will consent to and successfully complete a follow-up survey 30 days after their emergency department visit (t1). Equal numbers for t1 across all study arms enable comparisons for exploratory analyses of secondary endpoints. This estimate is based on the assumption that approximately 50% (*n* = 516) of the patients will agree to a follow-up interview, of which a further 17% (approximately *n* = 172 patients) will be unavailable or unable to complete the interview successfully for other reasons.

##### Participant observation of patient treatment paths and organizational processes in module 3

2.3.4.4

Participant observations (*n*∼10–15) will explore and document treatment paths of patients in the different navigation models of three study arms. These observations will result in digital protocols and digital patient flow diagrams. The aim of the participant observations is the in-depth exploration of model differences, patients' expressed treatment experience, their treatment paths, behavior and navigation within the respective care settings as well as provider-patient interaction. Participant observations will capture the structural and processual differences within and between study arms and hereby provide context-sensitive data for triangulation with the qualitative interviews and the multi-center cohort study, particularly with regard to model performance in terms of efficiency and patient safety, patient satisfaction (29) and measures of navigational health literacy (31) as well as health system responsiveness (30).

##### Provider online survey in module 3

2.3.4.5

An exploratory and anonymous quantitative online survey among a subgroup of health care providers working in the context of emergency care in Germany will be conducted, distributed by the professional networks of the authors. The survey aims to investigate which patient navigation models in emergency care and instruments are used at different locations in Germany and how providers assess the efficiency of these models.

##### Data analysis plan of module 3

2.3.4.6

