At t0, cost data from each participant will be mapped in standardized cost rates from the health care provider perspective. At t1, a cost-effectiveness analysis will be performed from the perspective of the German statutory health insurance to compare patient-reported health care utilization between the three study arms. Effects in terms of clinical endpoints (i.e., patient safety) will be compared with health care costs (utilization costs). Firstly, ANOVAs and/or if applicable ANCOVAs will be performed to identify significant cost differences between study arms. Patient characteristics may differ between the study arms. Thus, results are going to be adjusted with regard to possible confounders (e.g., age, triage level, comorbidities) to ensuring comparability. Secondly, average cost-effectiveness ratio (CER) and incremental cost-effectiveness ratio (ICER; comparing study arm 1 and 2 with standard emergency care of study arm 3) will be calculated to identify a dominant study arm in terms of cost-effectiveness. In a last and third step, bootstrapping can be conducted as sensitivity analysis to assess robustness of the results.

Qualitative content analysis will be applied to the digital observation protocols, following the analysis steps outlined in the data analysis plan for module 2 (25). In addition, the coding scheme for observation protocol analysis will be developed by two independent researchers using a random selection of protocols (10%–25% of the number of protocols) until there is acceptable overlap in coding (inter-coder reliability for qualitative content analysis; Krippendorff's *α* > 0.67), signifying that a validated scheme has been obtained (25, 42). The entire set of protocols is then coded. Quantitative data from the prospective multi-center cohort study is reported for individual observed patients in relation to the average of the entire survey population or specific subgroups to preserve anonymity. Results from the observation protocols are reported according to the standards for reporting qualitative research (27).

##### Data management plan of module 3

2.3.4.7

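### Table 2 and the analysis plan name different effect measures for the cost-effectiveness analysis, and the Table 2 version credits standard care with hypothetical diversion

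*Protocol article*

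**What the plan says.** In Table 2 (section 2.3.4.2), the row for costs and cost-effectiveness ends with "total costs in relation to primary outcomes". The table's primary block has a single entry, effectiveness of the care model, defined as "Proportion of patients that are actually treated (study arm 1 and 2)—or could have been treated (study arm 3) in an alternative outpatient emergency care", as opposed to treatment in the ED. Patient safety has its own row among the secondary outcomes.

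The data analysis plan of module 3 (section 2.3.4.6) describes the cost-effectiveness analysis differently: "Effects in terms of clinical endpoints (i.e., patient safety) will be compared with health care costs (utilization costs"). It then plans average cost-effectiveness ratios for the arms and incremental ratios "comparing study arm 1 and 2 with standard emergency care of study arm 3", with the aim of identifying a dominant arm.

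Section 2.3.4.7 states that the arm 3 primary endpoint rests on doctors' assessments of urgency and potential level of care. It is therefore a judgement about suitability and not an observed care path.

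**The concern.** An incremental cost-effectiveness ratio (ICER) needs one defined effect. The article gives two for the same analysis, so an analyst could follow either and claim to have followed the protocol.

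The two are not interchangeable. Under Table 2, arm 3 enters the ratio with the costs of care its patients received and with an effect that did not occur. Cost and effect in the comparator then describe different care paths, whereas in arms 1 and 2 they describe the same one. Because arm 3 is the reference for both ICERs, the mismatch enters both denominators. It also enters arm 3's average ratio.

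Cost-effectiveness is part of the stated objective and of research question 5, and the Discussion says that the findings may support ED managers and policymakers. A definition that can move a navigation model into the wrong quadrant of the cost-effectiveness plane should be settled before analysis.

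**Working it through.** **Inputs.** The planning rates for the primary endpoint are in section 2.3.4.3: arm 1, "Assumed frequency of the primary endpoint 30"%; arm 2, "Assumed frequency of the primary endpoint 50"%; arm 3, 70%. The comparator for both ICERs is arm 3 (section 2.3.4.6). Two quantities are not in the article: the proportion actually diverted in arm 3, called d here, and the cost differences between arms. I take d = 0 as the base assumption and show a range. For costs I use an illustrative 100 per patient in either direction.

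**Are 30/50/70% the plan's working rates?** Precision formula: n = 1.96² × p(1 − p) / 0.05².

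- p = 0.30: 322.7, rounded up to 323
- p = 0.50: 384.1, rounded up to 385
- p = 0.70: 322.7, rounded up to 323
- Total: 323 + 385 + 323 = 1,031, as stated.

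The stated 31 per arm also reproduces: a three-group chi-square test (2 df) at these rates with alpha 5% first reaches 80% power at n = 31 (power 0.812). The rates are therefore the plan's own.

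**Incremental effect under Table 2** (ΔE = arm rate − 0.70):

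- Arm 1: 0.30 − 0.70 = −0.40
- Arm 2: 0.50 − 0.70 = −0.20

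**Incremental effect on realised diversion** (ΔE = arm rate − d):

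| d, actual arm 3 diversion (assumed) | Arm 1 | Arm 2 |
|---|---|---|
| 0% | +0.30 | +0.50 |
| 10% | +0.20 | +0.40 |
| 20% | +0.10 | +0.30 |
| 30% | 0 | +0.20 |
| 40% | −0.10 | +0.10 |
| 50% | −0.20 | 0 |

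The sign is opposite to Table 2's as long as d is below 30% for arm 1 and below 50% for arm 2.

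**Consequence for the ICER** (cost difference / ΔE, with d = 0):

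| Cost difference vs arm 3 | Arm | ICER under Table 2 | ICER on realised diversion |
|---|---|---|---|
| −100 | 1 | −100/−0.40 = +250 | −100/0.30 = −333 |
| −100 | 2 | −100/−0.20 = +500 | −100/0.50 = −200 |
| +100 | 1 | 100/−0.40 = −250 | 100/0.30 = +333 |
| +100 | 2 | 100/−0.20 = −500 | 100/0.50 = +200 |

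In the first two rows, a model that saves money and diverts patients is classed as cheaper but less effective instead of dominant. In the last two, a costlier model that diverts patients is classed as dominated instead of costlier but more effective.

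**Consequence for the average ratio.** At equal cost per patient, arm 3's cost per unit of effect under Table 2 is 0.30/0.70 = 43% of arm 1's and 0.50/0.70 = 71% of arm 2's. With d = 0, standard care would look most efficient without having diverted anyone.

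**Under section 2.3.4.6.** With patient safety as the effect, the hypothetical arm 3 proportion does not enter the ratio, and none of these reversals arises.

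**The case against.** The strongest reply is that section 2.3.4.6 is the analysis plan and names patient safety explicitly, while Table 2 is only an overview. An analyst who follows the plan never meets the reversal. This stands: the reversal is a risk of one reading and not a feature of the plan as a whole. It does not remove the contradiction. Table 2 is where the outcomes are defined, and its wording cannot be stretched to cover safety, because the same table lists safety separately as secondary.

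It is also fair to say that the positive figures rest on an arm 3 diversion that the article does not give, and that the endpoint is secondary, measured at t1 (planned n = 344), with between-arm comparisons described as exploratory. Neither the primary analysis nor the sample size is affected.

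Some stronger readings are tempting but not supported:

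- **That the dominance verdict could be the exact opposite of the truth.** Only the effect sign changes, and the cost difference stays as it is. Moving from dominant to dominated needs both signs to change. Dominance can be missed, or wrongly awarded to arm 3, but not inverted.
- **That arms 1 and 2 are never compared.** Section 2.3.4.6 compares utilisation across all three arms, tests cost differences by ANOVA or ANCOVA and calculates average ratios. Only an ICER between arms 1 and 2 is not named.
- **That the ICER must mix perspectives or omit the index visit**, because t0 costs are "mapped in standardized cost rates from the health care provider perspective" and the t1 analysis takes the statutory insurer's view. The article presents these as separate steps, and section 2.3.4.1 says both sources feed the economic evaluation. How the index visit is valued is detail that an article may leave to the full plan.
- **That uncertainty is inadequately handled**, because "bootstrapping can be conducted as sensitivity analysis to assess robustness of the results" is worded as optional. This too is detail that may stand in the full plan.

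**Conclusion.** The point holds as an inconsistency with a conditional consequence. Two sections name different effects for one analysis, and no text reconciles them. If Table 2 is followed, the planned effect differences are −0.40 and −0.20 in favour of standard care, against +0.30 and +0.50 on realised diversion.

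This size rests on three things: that the Table 2 definition is used, that the planning rates are roughly right, and that arm 3 actually diverts few patients (below 30% for the arm 1 comparison, below 50% for arm 2). The 0% used for the positive figures is an assumption. The sign of the ICER itself also depends on cost differences that the article does not give.

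It should be corrected before the economic analysis, but as a secondary, exploratory endpoint it ranks below the problems that must be fixed for the trial's main conclusion.

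**What to change.** Name the same effect measure in Table 2 and in section 2.3.4.6. The simplest way is to amend the Table 2 row so that costs are related to the patient-safety endpoint that the analysis plan already names. Table 2 defines that endpoint identically for all arms.

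If a diversion-based ratio is also wanted, use diversion actually observed in every arm, arm 3 included. Do not set arm 3 to zero by definition, because any diversion would then count as a gain by construction. In either case, state that the hypothetical arm 3 proportion is excluded from both the ICER and the average ratio. It can still be reported descriptively.

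The cost is a change of wording in one table row and one sentence in the analysis plan. The safety option needs no new data. The diversion option needs the actual care path of arm 3 patients to be extracted; the article plans documentation of patient flows and routine data at the sites, so this should be a small addition.

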The power calculation is based on the primary endpoint—effectiveness of the care model, which is operationalized as the proportion of patients that are treated or could have been treated (study arm 3) in an alternative care structure other than regular ED care: A total sample size of 1,031 patients was confirmed to be recruited among the six study centers. The primary endpoint will be collected based on documented patient flows by study personnel and from secondary data of the respective study centers. The final approach needs to be adapted to local data availability at the study sites. The assumptions on the frequencies of the primary endpoint do not refer to all ED patients, but to the population matching the inclusion and exclusion criteria of the study which is estimated at 50% of all ED patients, based on scientific literature (35, 36). We assume that different proportions of patients with clinically low-acuity consultation needs will be treated in the three different patient navigation models. Assumptions for power calculation purposes were derived from scientific literature (1–7, 9, 37–41) and expert opinion: Study arm 1) The hospital-owned separate outpatient care facility within the ED premises or on the hospital grounds is suspected to lead to a reduction of 30% of ED visits; Study arm 2) Approximately 50% of all ED cases are assumed to be treated by the urgent care practice of the Regional Association of SHI Physicians at the ED location; Study arm 3) The proportion of patients in standard care who could potentially be treated in an alternative care structure is estimated at 70%. Therefore, to detect differences between study arms with a power of 80% and an alpha error of 5%, a sample size of *n* = 31 patients per study arm is required. Despite the low number of participants to determine the difference between study arms, we still aim for a higher precision to estimate the frequencies of the primary endpoint in the study arms. A precision of 5% based on the binomial 95% confidence interval is assumed. This results in different sample sizes per arm:

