Descriptive analyses will be performed among the total patient cohort and within the study arms for patient characteristics, as well as for primary and secondary endpoints. Relative and absolute frequencies will be reported for categorical variables, whereas for quantitative variables mean and standard deviation will be reported in case of normal distribution, median and inter quartile ranges for not normally distributed variables. The chi-square test will be used to investigate differences between study arms for categorical variables, while an analysis of variance (ANOVA; in case of normal distribution) or Kruskal–Wallis-Test (in case of no normal distribution) will be used to detect differences between study arms for quantitative variables. The evaluation of the primary endpoint—effectiveness (i.e., proportion of patients who actually were or potentially could be treated in the alternative outpatient emergency care model) will be carried out using a chi-square test and binomial 95% confidence intervals. Furthermore, factors associated with primary and secondary endpoints will be investigated. For continuous endpoints, analysis of covariance (ANCOVA) will be applied while binary endpoints will be analyzed by logistic regression or Poisson regression analyses. Survival analyses will be performed using Cox regression and Kaplan–Meier analysis. In case of significant associations between socio-demographic variables and secondary outcomes, a stratified analysis will be conducted. Non-parametric methods are used depending on the distribution of variables. Generalized linear mixed models (GLMM) and generalized estimating equations (GEE) are used for longitudinal data. In these analyses, *p*-values are interpreted exploratively, not corrected for multiple testing, and appropriate effect size measures are used.

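### The 5-point precision, the n = 31 and the primary chi-square test hold for comparing navigation models only if EDs within an arm do not differ

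*Protocol article*

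**What the plan says.** Section 2.2 defines the arms by what exists at a hospital: a hospital-owned outpatient unit, an SHI practice located at the ED, or a standard-care ED. Section 2.3.4.3 (Power calculation in module 3) spreads the cohort over six sites: "A total sample size of 1,031 patients was confirmed to be recruited among the six study centers". For the comparison of arms, "with a power of 80% and an alpha error of 5" per cent, it states that "31 patients per study arm is required". It then raises the numbers to gain precision within each arm: "A precision of 5% based on the binomial 95% confidence interval is assumed". This gives 323, 385 and 323 patients for assumed frequencies of 30%, 50% and 70%, a total of 1,031.

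Section 2.3.4.6 (Data analysis plan of module 3) says that the evaluation of the primary endpoint "will be carried out using a chi-square test and binomial 95% confidence intervals". Methods for correlated data appear once: "Generalized linear mixed models (GLMM) and generalized estimating equations (GEE) are used for longitudinal data". Site is not named as a cluster, and no ICC or design effect is given. Adjustment for confounders is described only with the cost analysis.

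**The concern.** Patients at one ED share its staff, triage practice, opening hours and redirection criteria, so their outcomes are likely to be correlated. If each ED belongs to one arm, the comparison of models rests on six units, not on 1,031. The article itself leads one to expect differences between sites. The Introduction calls the redirection instruments locally diverse. Section 2.3.4.4 sets out to document differences within as well as between arms. Section 2.3.4.3 says that endpoint collection must be adapted to the data available at each site.

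A binomial interval and a patient-level chi-square test set all this variation to zero. The risk is that ordinary differences between hospitals are reported, with narrow intervals, as effects of the navigation model. The article intends these results to inform ED managers and policymakers.

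**Working it through.** **1. The plan's own figures.** With independent patients, n = 1.96² × p(1−p) / 0.05².
- p = 0.30 or 0.70: 3.8415 × 0.21 / 0.0025 = 322.7, so 323.
- p = 0.50: 3.8415 × 0.25 / 0.0025 = 384.1, so 385.
- Sum: 323 + 385 + 323 = 1,031.

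The 31 per arm matches the three-arm chi-square test with 2 df. The effect size is w² = variance of (0.3, 0.5, 0.7) / 0.25 = 0.02667 / 0.25 = 0.1067. The noncentrality is 93 × 0.1067 = 9.92, which gives 81.2% power (79.8% at n = 30). The arithmetic is right under independence.

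**2. Inputs that the article does not give.** These are assumptions: two EDs per arm, each ED in one arm, and an ICC from 0.001 to 0.05. At p = 0.5 the between-site SD is √(0.25 × ICC), which is 1.6 points at ICC 0.001, 5 points at 0.01 and 11 points at 0.05.

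**3. Half-width for arm 2** (n = 385, p = 0.5, m = 385/2 = 192.5 per site). The design effect is DE = 1 + 191.5 × ICC, and the half-width is q × √(0.25 × DE / 385). Here q is 1.96, or 3.182 for t with 3 df (six sites minus three arm means), which matches a site-level analysis.

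| ICC | DE | ± points, q = 1.96 | ± points, t on 3 df |
|---|---|---|---|
| 0.001 | 1.19 | 5.5 | 8.9 |
| 0.005 | 1.96 | 7.0 | 11.3 |
| 0.01 | 2.92 | 8.5 | 13.8 |
| 0.02 | 4.83 | 11.0 | 17.8 |
| 0.05 | 10.58 | 16.2 | 26.4 |

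For arms 1 and 3 the half-widths with 1.96 are 5.4, 6.7, 8.1, 10.3 and 15.0 points. More patients do not solve this. As n grows, the half-width with two sites tends to 1.96 × √(0.25 × ICC / 2), which is already 6.9 points at ICC 0.01.

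**4. Error rate of the planned test.** Beta-binomial simulation with six sites, equal true proportions of 0.5 and the planned arm sizes:

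| ICC | Chi-square rejects a true null | Arm 2 binomial interval covers |
|---|---|---|
| 0 | 5% | 95% |
| 0.001 | 8% | 92% |
| 0.005 | 20% | 83% |
| 0.01 | 33% | 74% |
| 0.02 | 51% | 62% |
| 0.05 | 74% | 44% |

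A hand check agrees. With 2 df the rejection rate is about exp(−2.996 / DE), where DE = 1 + (1,031/6 − 1) × ICC. At ICC 0.01, DE = 2.708 and exp(−1.106) = 0.33.

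**5. Does the n = 31 survive?** With 15.5 patients per site, DE = 1 + 14.5 × ICC. By the design effect alone, power falls from 81% to 75% at ICC 0.01 and to 56% at 0.05.

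**6. The alternative test.** An F test on the six site proportions (2 and 3 df) keeps its 5% level in the same simulation. Its power for 30/50/70% is about 91%, 76% and 47% at ICC 0.01, 0.02 and 0.05.

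**The case against.** - **The inputs are assumed.** The article gives no ICC and no allocation of sites to arms, and the result depends strongly on both. At ICC 0.001 the loss is small: 5.5 points instead of 5 with the normal quantile, and 8% instead of 5%. This stands, and it is why the point is conditional.
- **Assignment by ED is inferred.** No sentence says that each ED belongs to exactly one arm. If a site contributed to two arms, the formulas above would not apply as written. Section 2.2 makes one arm per ED the natural reading.
- **A narrower target is legitimate.** For the patients of these six EDs, with sites regarded as fixed, the binomial interval is valid. This stands, but the research questions ask how the models differ, and the Discussion offers the results for adapting or implementing models.
- **The p-values are exploratory.** It is unclear whether that sentence covers the primary test. In any case, the label does not widen an interval or restore a stated precision.
- **The assumed differences are large.** If 30/50/70% is true, the arms will usually come out in the right order: in about 99.9%, 99% and 92% of simulated trials at ICC 0.01, 0.02 and 0.05. The damage is mainly to interval width and attribution.

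A reader might infer that the stated precision and error rate are certainly missed by a wide margin. The document does not support that, because the size rests on an ICC and a site split that it does not report.

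**Conclusion.** The point holds in conditional form. The article itself fixes the sample-size formula, the primary test and the interval, so this is not detail left to an analysis plan. All three assume independent patients, while the arms appear to be site-level models at six EDs. As statements about models, the 5-point precision, the n = 31 and the 5% error rate hold only with no between-site variation within an arm.

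The size depends on assumptions that the document does not supply: two EDs per arm, one arm per ED and the ICC. The effect runs from minor at ICC 0.001 on the normal-quantile scale to severe from about ICC 0.01. Even at ICC 0.001, an interval on 3 df is about 9 points either side.

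**What to change.** - **Section 2.3.4.6:** Report the proportion at each of the six sites. Base arm comparisons on a site-level test, which is an F test with 2 and 3 df if there are two sites per arm. Use a GEE or mixed model with site as cluster only with a small-sample correction, because six clusters are few.
- **Section 2.3.4.3:** State how sites are allocated to arms. Say that the 5-point precision and the n = 31 apply only to the patients of these six EDs, or if sites within an arm do not differ. Give the wider half-widths over a stated, assumed ICC range, with the t quantile that matches the analysis.
- **Alternative:** Keep the binomial intervals, limit the conclusions to these sites, and do not attribute differences to the navigation model.

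This needs changes to wording and analysis and no extra patients. The cost is wider intervals, a less favourable stated precision, and lower power if sites vary much.

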1.Which patient navigation models in emergency care entailing navigating of eligible patients to an alternative care pathway or care setting are practised internationally? (module 1)2.What is the evidence for these models in terms of quality of care (care process or outcome quality, incl. patient satisfaction), patient safety, and cost-effectiveness? (module 1)3.Which patient navigation models in emergency care are practised in the pilot region of Berlin and in Germany? (module 2 & module 3)4.How do providers and patients qualitatively evaluate different patient navigation models in emergency care that are already practised in Berlin? (module 2 & module 3)5.How do different patient navigation models in emergency care practised in Berlin differ quantitatively in terms of efficiency, quality of care, patient safety, patient satisfaction, and cost-effectiveness? (module 3)6.Which urgency and level of care show patients assessed by ED doctors in standard care EDs included in the study? (module 3)7.How do the three included patient navigation models differ in terms of patient processing and care pathways, as well as patient experience (module 2 & module 3)?8.What recommendations can be derived for political decision-makers from the findings of questions 1–7 for future organisation of patient navigation models in emergency care? (module 4)

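### The planned cost-effectiveness ratios use arm 3 as the only comparator and leave out the arm 1 v arm 2 increment, so unless one arm strictly dominates both others they do not show which model is cost-effective

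*Protocol article*

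**What the plan says.** Research question 5 in the Introduction asks: "How do different patient navigation models in emergency care practised in Berlin differ quantitatively in terms of efficiency, quality of care, patient safety, patient satisfaction," and it adds cost-effectiveness to that list. The data analysis plan of module 3 (2.3.4.6) sets up a cost-effectiveness analysis from the statutory health insurance perspective "to compare patient-reported health care utilization between the three study arms".

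The analysis has three steps:

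- ANOVA or ANCOVA on costs across the arms, with adjustment for confounders.
- Ratios: "average cost-effectiveness ratio (CER) and incremental cost-effectiveness ratio", the latter "comparing study arm 1 and 2 with standard emergency care of study arm 3) will be calculated to identify a dominant study arm".
- Bootstrapping, as an optional sensitivity analysis for robustness.

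On the effect side, the same section says: "Effects in terms of clinical endpoints (i.e., patient safety) will be compared with health care costs (utilization costs"). Table 2 instead describes the measure as "total costs in relation to primary outcomes".

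The comparator, the statistics and their purpose are therefore stated in the text. An arm 1 v arm 2 ratio, an ordering of arms by cost and a net-benefit comparison are not.

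**The concern.** With three mutually exclusive options, the price of choosing an arm is its extra cost per extra unit of effect over the next-cheapest arm that is neither dominated nor extendedly dominated. That arm need not be standard care. Two ICERs against a common comparator do not display the trade-off between the two navigation models.

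Average CERs do not fill the gap. They divide total cost by total effect, so they say nothing about what an additional unit costs.

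The Discussion says the cost-effectiveness findings may support managers and policymakers in adapting or implementing navigation models. For a site weighing one model against the other, arm 1 v arm 2 is the relevant contrast, and it is the one missing from the ratios.

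**Working it through.** The documents state no cost, effect, ICER or threshold, so there is no figure to reproduce. All costs (C, euro), effects (E, proportion free of a safety event) and thresholds (λ, euro per event avoided) below are assumptions.

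Formulas: CER = C/E. ICER of arm i against arm j = (Ci − Cj)/(Ei − Ej). Net monetary benefit NMB = λE − C.

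**1. Both models dearer and safer than arm 3.** Arm 3: 400, 0.90. Arm 1: 450, 0.95. Arm 2: 550, 0.96.

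- Planned, arm 1 v 3: (450 − 400)/(0.95 − 0.90) = 1,000.
- Planned, arm 2 v 3: (550 − 400)/(0.96 − 0.90) = 2,500.
- Not planned, arm 2 v 1: (550 − 450)/(0.96 − 0.95) = 10,000, four times the planned figure for arm 2.
- For any λ between 2,500 and 10,000, arm 2 looks acceptable against arm 3 although arm 1 has the higher net benefit. At λ = 5,000, NMB is 4,300 (arm 1), 4,250 (arm 2) and 4,100 (arm 3).
- Average CERs: 400/0.90 = 444 (arm 3), 450/0.95 = 474 (arm 1), 550/0.96 = 573 (arm 2). The lowest belongs to the cheapest, least effective arm, although moving to arm 1 costs only 1,000 per event avoided.

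**2. Both models cheaper and safer than arm 3.** Arm 3: 400, 0.90. Arm 1: 350, 0.94. Arm 2: 300, 0.92.

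- Planned, arm 1 v 3: −50/0.04 = −1,250. Planned, arm 2 v 3: −100/0.02 = −5,000.
- Arm 1 v 2: 50/0.02 = 2,500. Arm 2 is best for λ below 2,500 and arm 1 above it, and neither dominates the other.
- Both planned ICERs are taken against a dominated comparator, and their size does not reveal the switch at 2,500. The lowest CER (300/0.92 = 326, arm 2) does not reveal it either.
- Average CERs also depend on how the effect is coded. Per event, arm 1 costs 350/0.06 = 5,833 and arm 3 costs 400/0.10 = 4,000, although arm 1 dominates arm 3.

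**3. A range instead of chosen points.** 200,000 random draws, with each arm's cost uniform on 200–600 and effect uniform on 0.80–0.98, independently:

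| λ | Lowest CER is the arm with highest NMB |
|---|---|
| 500 | 97% |
| 1,000 | 88% |
| 2,500 | 69% |
| 5,000 | 56% |
| 10,000 | 48% |

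In 33% of draws one arm strictly dominated both others, and the lowest CER (effect coded as a benefit) then always pointed to it. In 11% of draws arms 1 and 2 both dominated arm 3. In about half of those, one of the two also dominated the other, and the more negative ICER identified the dominating arm 50% of the time, no better than chance.

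**4. Can a dominated model look better than the other in the planned ICERs?** Take arm 3 as cheapest and least effective.

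- If arm 2 strictly dominates arm 1, arm 1 has the larger cost increment and the smaller effect increment over arm 3, so its ICER is always worse. Example: arm 1 at 550, 0.92 and arm 2 at 500, 0.96 give 150/0.02 = 7,500 and 100/0.06 = 1,667.
- If arm 1 is extendedly dominated, ICER(1 v 3) exceeds ICER(2 v 1). ICER(2 v 3) is a weighted average of those two, so it lies below ICER(1 v 3).

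In this configuration the planned ICERs never put a dominated or extendedly dominated model ahead of the other model.

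**The case against.** The plan speaks of a dominant arm. It does not promise to rank the arms or to find the best one, and strict dominance can be read from arm-level mean costs and effects. Comparing each model with standard ED care is a stated aim of the study (Abstract, Discussion), so arm 3 is a natural comparator. Costs are compared across all three arms with adjustment, and the arm 1 v arm 2 increment is a simple difference of means that will exist anyway. Thresholds and acceptability analyses may sit in a fuller plan. The endpoint is secondary, and recommendations come from triangulation and a symposium, not from an ICER rule.

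Most of this stands and limits the point. A reader might infer that the plan would recommend a model that the other one dominates. The documents do not support that: step 4 of the working rules it out for the ICERs when arm 3 is cheapest and least effective, and the text nowhere says that negative ICERs will be compared by size. Nor does it name the average CER as a sole decision criterion. The lack of a threshold is not held against a condensed article.

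The objection does not remove the mismatch. The text names the ratios and their purpose, and they omit one of the three contrasts among the arms. If no arm strictly dominates both others, a reader of the planned output does not learn what it costs to prefer one model to the other.

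**Conclusion.** The point holds as a minor one. The planned ratios answer whether each model is worth its cost compared with standard care. They do not answer which model is cost-effective among three, unless one arm is both cheapest and most effective.

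The ICER of the costlier model can understate the price of choosing it over the other model. Under the assumed inputs this is 2,500 against 10,000, and the fourfold gap rests on an assumed effect difference of only 0.01. Average CERs can favour the cheapest, least effective arm, and negative ICERs carry no ranking information. The percentages in the working depend on the assumed ranges and are no forecast for this study.

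To conclude that the best arm cannot be identified would be too strong. The limit applies to the planned ratios, not to the data.

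**What to change.** In 2.3.4.6, replace the ratio step with a full incremental analysis:

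- Order the three arms by confounder-adjusted mean cost and remove dominated and extendedly dominated arms.
- Report each remaining arm's ICER against the next-cheapest remaining arm. Alternatively, report incremental net benefit for all three arms over a range of thresholds.
- Give the arm 1 v arm 2 contrast explicitly, with its uncertainty from bootstrap resampling of the three arms jointly.
- Keep the ICERs against arm 3 as supplementary output and the average CERs as description only.
- State one effect measure and its coding, since 2.3.4.6 and Table 2 differ.

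The cost is a change of wording and a little more computation on data already planned. The arm 1 v arm 2 estimate will be imprecise. With 344/3, about 115 patients per arm at t1, and the assumed effects of 0.95 and 0.96, the standard error of the difference is √(0.95 × 0.05/115 + 0.96 × 0.04/115) ≈ 0.027, against a difference of 0.01. This favours net benefit with intervals over a bare ratio.
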